### Study objectives and hypothesis

1.1

The objective of this two-arm randomized controlled trial is to compare the effectiveness of a character-strengths based coaching intervention on wellbeing of ASHAs relative to routine health system supervision that ASHAs already receive.

The hypotheses include:A)Primary hypothesis: ASHAs who receive the proposed coaching intervention (in addition to routine supervision) will show greater wellbeing than those who receive routine supervision alone.B)Secondary hypotheses:a)ASHAs who receive the proposed coaching intervention (in addition to routine supervision) will show greater reduction in burnout and increase in motivation scores, than those who receive routine supervision alone.b)ASHAs who receive the proposed coaching intervention will show greater improvement in service delivery indicators (e.g., daily service contacts for routine services such as prenatal check-ups and conducting brief psychological treatment sessions for depression) than those who receive routine supervision alone.c)ASHAs who receive the proposed coaching intervention will show greater patient satisfaction for depression care services, and rates of remission in their patients' depression severity at endpoint, than ASHAs who receive routine supervision alone. (Note: All ASHAs prior to baseline assessment will be trained to deliver the brief psychological treatment for depression, see Fig. 1)

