***Service delivery measures***	Routine service delivery indicators as collected by the health system (e.g., related to antenatal checkups done, post-natal visits conducted, immunizations done)	A survey form will be generated with a list of routine ASHA performance indicators in consultation with the district health team. The form will include indicators for various services such as antenatal and postnatal care, reproductive health, and immunization. Examples of specific indicators include proportion of antenatal checkups expected out of total pregnant women in the ASHA's catchment area (for a fixed period e.g., a reporting month) and proportion of antenatal checkups completed out of total expected checkups.	Given the evidence-base, improved wellbeing can contribute to improved service delivery as reflected in changes in observed service delivery indicators [[65], [66], [67], [68], [69]].	Percentages of services delivered will be significantly higher in the intervention arm relative to the control arm	Data will be collected directly from the district health team for the period starting from baseline assessment to end of 6-month follow-up assessment.
		With respect to depression care, data on number of HAP sessions delivered, patients with completed treatment and patient dropouts will be gathered from ASHAs.			Number of HAP sessions delivered; number of patients with completed treatments; and number of patient dropouts will be compared between arms at 3-month and 6-month follow-up

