***Cost of Intervention delivery***	Cost of ASHA's participation in the workshop (survey) and cost of participation in remote coaching (survey)	We will assess costs incurred by ASHAs due to their participation in their respective intervention workshop and remote coaching activities. A post-workshop questionnaire (on day-5) and a remote coaching questionnaire (during the 4th and 8th coaching call, covering data of the previous calls) will be developed and administered to capture individual-level costs incurred by ASHAs, such as items covering their workshop/remote coaching time, workshop travel time, workshop travel costs, smartphone data packs (remote coaching) and food/refreshment costs (residential workshop).	If the primary outcome results show significant differences in mean authentic happiness scores between arms at 3-month follow-up as seen in the pilot study (under peer review), estimating the cost of delivering such an intervention will have significance from the point of view of health system adoption.	Data only collected in the intervention arm	Post-workshop questionnaire administered to ASHAs on day-5 of each intervention workshop batch.
					Remote coaching questionnaire administered to ASHAs during the 4th and 8th coaching call, covering data of the previous calls.

With respect to depression care delivery, we will calculate the number of ASHAs’ HAP sessions, on a weekly basis. At 3-month and 6-month follow-up, we will compare the numbers of these HAP sessions between arms (Note: HAP treatment durations range from 6 weeks to 3 months), in addition to numbers of patients with closed (completed) treatments and drop-outs.

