### Sample size estimation

2.6

In the absence of trials looking at the effectiveness of interventions aimed at improving wellbeing among community health workers in India, we referred to methodologically similar designs for calculating the sample size [[55], [56], [57]]. We will measure the change in wellbeing, pre- and post-intervention, in terms of mean happiness scores on the Authentic Happiness Inventory (AHI). We initially assumed a significant between-group difference of 0.19 points (effect size: 42 %) for the mean happiness scores at 3-month follow-up for the intervention arm (mean: 3.35, SD: 0.43) and control arm (mean: 3.16, SD: 0.48). With 90 % power and a two-sided α of 0.05, 122 ASHAs per arm are required to measure this difference by the independent group *t*-test.

The patient-outcome of depression severity will be measured by the nine-item Patient Health Questionnaire (PHQ-9) [32]. We will assess the proportion of patients who show ‘early remission’ or attain a post-treatment score of <10 [58] and compare these remission rates between the two arms at the patient's 3-month follow-up assessment. For the patient-outcome, we will refer the early remission rates in the PRIME Cohort study [58] due to its contextual similarity to our trial and assume rates of 40 % and 60 % in the control and intervention arm respectively. With a two-sided α of 0.05, and 80 % power, we will need 97 patients with depression per arm. Therefore, each of the 122 ASHAs per arm will be required to provide HAP sessions to at least 1 patient, accounting for dropouts from treatment and loss to follow-up.

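### Patient drop-outs from HAP are compared between arms as raw numbers, so the intervention arm can appear to have more drop-out merely because its ASHAs start more patients

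*Protocol article*

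**What the plan says.** The Service delivery measures row of Table 2 states: "Number of HAP sessions delivered; number of patients with completed treatments; and number of patient dropouts will be compared between arms". The comparison is made at months 3 and 6. The paragraph after the table (section 2.4.2) repeats the count form: HAP sessions are compared "in addition to numbers of patients with closed (completed) treatments and drop-outs". The data items listed are: "data on number of HAP sessions delivered, patients with completed treatment and patient dropouts will be gathered from ASHAs". The number of patients who started HAP is not among them.

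Routine services in the same row do have a denominator, for example "proportion of antenatal checkups completed out of total expected checkups". The hypothesis cell of that row reads "Percentages of services delivered will be significantly higher in the intervention arm relative to the control arm", but no percentage is defined for any HAP item and no direction is stated for drop-outs.

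Two other places bear on volume. Secondary hypothesis b (section 1.1) expects better service delivery in the intervention arm, including "daily service contacts for routine services such as prenatal check-ups and conducting brief psychological treatment sessions for depression". Section 2.6 says that "each of the 122 ASHAs per arm will be required to provide HAP sessions to at least 1 patient", which sets a minimum and no maximum.

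**The concern.** The number of drop-outs is the number of patients started multiplied by the drop-out risk. A comparison of counts therefore mixes how many patients an ASHA takes on with how well she keeps them. Volume is settled after randomisation, and the intervention may well change it. If coached ASHAs start more patients and keep them equally well, their arm shows more drop-outs, and a reader would naturally take that as poorer retention.

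The cut-off adds some ambiguity. HAP treatment lasts from 6 weeks to 3 months (text after Table 2), so at month 3 or 6 some patients will have neither completed nor dropped out. Section 2.3.3 requires ASHAs to have delivered HAP sessions before baseline, and the outcome text does not say whether patients started before randomisation count.

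What is at stake is the reading of one secondary service-delivery indicator in a trial meant to inform adoption by the health system.

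**Working it through.** **Plan's own figure.** The article states no figure for HAP drop-outs, so there is none to reproduce on this outcome. The 122 ASHAs per arm (section 2.6) used below does reproduce. The pooled SD is √((0.43² + 0.48²)/2) = 0.4557 and the difference is 0.19. With two-sided α 0.05 and 90% power, the t-test needs 121.85, i.e. 122 per arm.

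**Inputs.**
- From the article: 122 ASHAs per arm, 1:1 allocation, at least 1 patient per ASHA.
- Assumed, because the article gives none: m = 1, 3 or 6 patients per control ASHA; drop-out risk d = 20% in both arms; intervention ASHAs start r = 1.25 or 1.5 times as many patients; a two-sided 5% test on the counts. The article names no test for this outcome.

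**Formulas.** Expected drop-outs are 122 × m × d (control) and 122 × m × r × d (intervention). Treating the totals as Poisson, z = difference / √(sum). The chance of a significant excess in the intervention arm is P(Z > 1.96 − z).

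| m | r | Control v intervention | z | Chance of significant excess |
|---|---|---|---|---|
| 1 | 1.25 | 24.4 v 30.5 | 6.1/√54.9 = 0.82 | about 13% |
| 3 | 1.25 | 73.2 v 91.5 | 18.3/√164.7 = 1.43 | about 30% |
| 6 | 1.25 | 146.4 v 183.0 | 36.6/√329.4 = 2.02 | about 52% |
| 1 | 1.5 | 24.4 v 36.6 | 12.2/√61.0 = 1.56 | about 35% |
| 3 | 1.5 | 73.2 v 109.8 | 36.6/√183.0 = 2.71 | about 77% |
| 6 | 1.5 | 146.4 v 219.6 | 73.2/√366.0 = 3.83 | about 97% |

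Retention is identical in every row. With r = 1 the chance is the nominal 2.5% in that direction.

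**Check by simulation.** In 2000 trials per scenario, patients per ASHA were Poisson and drop-outs binomial, and drop-out counts per ASHA were compared by t-test, with m = 1, 2 or 4 and d = 20, 30 or 40%. A significant excess in the intervention arm appeared in 2–3% of trials at r = 1, 13–64% at r = 1.25 and 32–99.6% at r = 1.5. When drop-outs were instead divided by patients started, the two-proportion test rejected in about 4–6% of trials in every scenario.

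Both calculations leave out extra variation in volume between ASHAs, which would lower the count-based chances, and clustering of drop-out within ASHA, which the proportion test would have to allow for.

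**Completions.** These scale by the same r. With m = 2, d = 30% and r = 1.5, expected completions are 122 × 2 × 0.7 = 170.8 v 256.2 at an unchanged completion rate. That is a real difference in output per randomised ASHA.

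**The case against.** The strongest reply is that the premise is not stated. Hypothesis b speaks of sessions, not patients started. Each patient is due 6–8 sessions (section 2.3.2), so more sessions could come from better continuation, which would lower drop-outs. This stands: the distortion is conditional on patients started differing between arms. A reader might infer that a successful intervention must show more drop-outs, and the documents do not support that.

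A reader might also infer that the completion count is invalid and should be replaced. It should not be. With ASHAs randomised 1:1, completed treatments per randomised ASHA is a legitimate measure of volume, and misleads only if read as retention.

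Third, the drop-out comparison is not unreadable. Drop-outs as a share of closed treatments can be derived from the listed items: in the example above, 73.2/(73.2 + 170.8) and 109.8/(109.8 + 256.2) are both 30%. Enrolled patients by arm will also be visible from the consent process (section 2.3.3) and the reports to the IRB (section 2.9). This softens the point. But the comparison the plan names is still the raw count, and the share of closed treatments leaves out patients still in treatment.

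Fourth, volumes, drop-out risk and test are all assumed. At the article's minimum of 1 patient per ASHA, the chance is about 13% or 35%, not the larger figures. That is why the whole range is shown.

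Finally, patients started after randomisation is itself a denominator that the intervention can alter, so the proportion loses some of the protection of randomisation. That is a reason to add it to the counts rather than substitute it.

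**Conclusion.** The point holds in a limited form. The article fixes the drop-out outcome as a count in two places, so this is not a detail left open for an analysis plan. A count cannot separate volume from retention. If intervention ASHAs start more patients, drop-outs can appear higher in their arm at identical retention. On the stated assumptions (122 ASHAs per arm, 1 to 6 patients per control ASHA, 20% drop-out in both arms, Poisson totals), the chance of a spurious significant excess is about 13–52% with 25% more patients and about 35–97% with 50% more. If patients started do not differ, there is no distortion.

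The importance is moderate. This is one indicator within a secondary outcome, no hypothesis in section 1.1 names drop-out, and the primary AHI analysis and the comparison of remission rates are unaffected.

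**What to change.** Amend the Service delivery measures row of Table 2 and the paragraph after it:

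- Keep the numbers of HAP sessions and completed treatments per randomised ASHA as volume measures.
- Add the number of patients who started HAP, by arm.
- Compare drop-out, and secondarily completion, as a proportion of patients who started HAP after the ASHA's randomisation, with an analysis that allows for clustering by ASHA.
- Show patients still in treatment at the month-3 or month-6 cut-off as a separate category.
- State that the proportions are read alongside the counts, because the number started may itself be affected by the intervention.

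The cost is mainly wording. Patients started is not a listed item, but it should be derivable from the HAP session data that the HAP supervisors retrieve through the learning management system (section 2.3.2). The sponsor should confirm that these records carry a start date for each patient. No extra participant contact should be needed.

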#### Participant training on the evidence-based brief psychological treatment for depression

2.3.2

In the sampling frame, we will sample a target of 330 ASHAs for orientation and training on the Healthy Activity Program (HAP), an evidence-based brief psychological treatment for community-based care for people identified with depression [29]. We will use simple random sampling (SRS) without replacement for this purpose. SRS will offer maximum sample diversity, equal chance of representation of all ASHAs, high internal and external validity and ease of data analysis [33,34]. This is about 25 % higher than the required number of ASHAs (n = 244, refer 2.6) to account for potential attrition/loss to follow-up and health workers who may decline to participate in HAP training and/or further study processes i.e., baseline assessments, intervention activities and outcome assessments (Fig. 1). The sampled ASHAs will be assigned unique participant IDs, which will be used to contact them regarding trial recruitment. These IDs will stay with the ASHAs throughout the trial period. The research team will call the sampled ASHAs from the list to invite them to participate in the study, starting with an in person orientation on the digital training platform [29] and training for delivering the HAP. After orientation and training completion, ASHAs will start community screening for depression and delivery of 6–8 HAP sessions (every ∼8–15 days) for each patient. ASHAs will also receive fortnightly peer group supervision for the delivery of HAP as documented in previous contextual studies [29,35]. A dedicated team of HAP supervisors, through the MindScroll Learning Management System [36], will supervise the ASHAs’ challenges in delivering HAP, and also retrieve the data on delivery of HAP sessions.

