#### Baseline assessment

2.3.3

ASHAs who have completed HAP training, delivered HAP sessions to patients, and received peer group supervision for their delivered HAP sessions, will be invited to come to their nearest community/primary health center to participate in a group information session. A trained research team member will explain the goals of the study to the group and what their participation will involve, depending on the (subsequent) arm allocation. We will provide an overview of the time required to participate in either of the experimental conditions (intervention or control arm) and the completion of study outcome assessments. ASHAs who are interested and willing to participate will meet with a research assistant, who will confirm eligibility and review a study information sheet and consent form with them. The research assistant will ensure that the ASHA has fully read and understood the participant information sheet and consent form before obtaining written informed consent. We will document the number of ASHAs who are eligible to participate, who decline participation (with reported reasons) and who are lost to follow-up.

After consenting, ASHAs will complete the baseline assessment. A research assistant will collect demographic information (including, for example, age, years of work experience, education level, and ownership of assets), and participants will self-report the primary outcome of wellbeing (i.e., authentic happiness), and additional measures (i.e., ASHA's affect, self-efficacy, flourish, burnout, motivation, physical health symptoms and quality of life). The baseline assessment will require approximately 2–3 h to complete. ASHAs will take short breaks at any time during the assessment and will be provided with snacks. The research assistant will be present throughout the process to respond to queries and ensure that ASHAs are able to complete the assessment forms.

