#### Randomization

2.3.4

Following the baseline assessment, ASHAs will be randomly allocated (1:1) to one of two study arms using Stata-17 [37]. Stata allows the researcher to set the ‘seed’ used to start the random number generator (RNG) process, so that it is reproducible; and it tracks the ‘state’ which the RNG is in before each command is run. Therefore, with each command, the RNG ‘state’ within the seed changes, which maintains the randomness of each subsequent command. Since we will train all ASHAs on HAP prior to randomization, any potential effects of mental health training on ASHAs' own wellbeing will be balanced between the arms. Prior to randomization, we will first stratify ASHAs who will complete baseline assessments using age (in years) and education level (number of total years of education), as these are some of the variables that may affect an ASHA's absorption of the intervention content and potentially affect the wellbeing outcome. Stratification will ensure that age- and education-distribution between the arms is balanced. Research team will inform all ASHAs (regardless of arm allocation) of the scheduled dates of their next (1-month) follow-up assessment, and so on for 3-month and 6-month follow-ups. Further, a separate research assistant will call the ASHAs and confirm their availability to attend the intervention residential workshop (if allocated to the intervention arm). ASHAs allocated to the intervention arm will receive the workshop within 7–10 days of baseline assessment.

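### HAP session numbers are compared at 3 and 6 months with no pre-randomisation count and no start for counting named, which costs some precision and does not match the hypothesis of greater improvement

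*Protocol article*

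**What the plan says.** Secondary hypothesis (b) in section 1.1 states that ASHAs in the coaching arm "will show greater improvement in service delivery indicators". One of its examples is "conducting brief psychological treatment sessions for depression".

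Section 2.3.3 invites to the baseline assessment those "ASHAs who have completed HAP training, delivered HAP sessions to patients, and received peer group supervision for their delivered HAP sessions". Section 2.3.4 places randomisation after that: "Following the baseline assessment, ASHAs will be randomly allocated (1:1) to one of two study arms". Section 2.3.2 says that HAP supervisors, working through the learning management system, "will supervise the ASHAs’ challenges in delivering HAP, and also retrieve the data on delivery of HAP sessions".

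The text after Table 2 in section 2.4.2 says that the team will calculate the number of ASHAs' "HAP sessions, on a weekly basis", and then: "At 3-month and 6-month follow-up, we will compare the numbers of these HAP sessions between arms". The service delivery row of Table 2 gives the same two time points for sessions, completed treatments and dropouts, and says that these data come from the ASHAs. The self-report questionnaire measures in Table 2 all list a baseline assessment; the HAP measures do not. Section 2.8 gives no model for session counts and neither specifies nor excludes covariates.

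**The concern.** The hypothesis is about improvement, and the trial generates a pre-randomisation value for each ASHA on this outcome. The stated comparison uses follow-up numbers only. This differs from the district indicators such as antenatal care and immunisation, which are collected only from baseline onward. For HAP sessions, earlier activity exists and is not put to use.

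Two things are at stake. ASHAs probably differ in how many sessions they deliver, and any stable part of that difference stays in the error term unless the earlier rate is adjusted for. A real coaching effect is then somewhat easier to miss. Also, because delivery starts before allocation and no start is given for the count, the outcome itself is not fully defined.

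**Working it through.** **The plan's own figure.** The only ASHA-level sample size is for the Authentic Happiness Inventory (section 2.6): difference 0.19, SDs 0.43 and 0.48, 90% power, two-sided alpha 0.05. The pooled SD is sqrt((0.43² + 0.48²)/2) = 0.4557, so the effect is 0.19/0.4557 = 0.417 SD. The normal approximation gives 121 per arm; the t-test gives 121.85, rounded up to 122. The stated 122 reproduces, but it says nothing about power for HAP sessions.

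**Effect of adjustment.** Take 122 per arm and express the session outcome in SD units. The effect that an unadjusted comparison detects with 80% power is (1.960 + 0.842) × sqrt(2/122) = 0.359 SD. Adjusting for a baseline value with correlation rho multiplies the variance by 1 − rho², so

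power = Φ((0.842 + 1.960)/sqrt(1 − rho²) − 1.960).

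A raw change score multiplies the variance by 2(1 − rho) instead. The document gives no rho, so it is an assumption, shown over a range:

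| rho | 1 − rho² | power, adjusted | unadjusted n per arm with the same precision, 122/(1 − rho²) | power, change score |
|---|---|---|---|---|
| 0.1 | 0.99 | 80.4% | 123 | 55.1% |
| 0.2 | 0.96 | 81.6% | 127 | 60.1% |
| 0.3 | 0.91 | 83.6% | 134 | 65.8% |
| 0.5 | 0.75 | 89.9% | 163 | 80.0% |
| 0.7 | 0.51 | 97.5% | 239 | 95.1% |

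From 80%, covariate adjustment gains 1.6, 3.6, 9.9 and 17.5 points at rho 0.2, 0.3, 0.5 and 0.7. A change score does worse than the follow-up-only comparison whenever rho is below 0.5.

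**Which rho is plausible.** Section 2.3.2 describes courses of 6–8 sessions per patient, about 8–15 days apart. Section 2.6 requires at least one patient per ASHA. A capped course limits the correlation, because sessions delivered before randomisation use up part of a patient's course. Capped courses were simulated under two sets of assumptions. The first set had the first patient started before randomisation, 4–8 weeks before and about 13 weeks after it, and gamma variation of shape 2–4 in further patients. The correlations of log counts were:

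| Mean patients per ASHA | First set | Second set |
|---|---|---|
| 1.5 | 0.04–0.16 | 0.17–0.31 |
| 2 | 0.23–0.31 | 0.34–0.46 |
| 3 | 0.39–0.45 | 0.44–0.58 |

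In the first set, exactly one patient per ASHA gave a negative correlation, an artefact of course timing. Larger caseloads raise rho. The document gives no caseload, so about 0.2–0.5 is a reasoned range and not an estimate.

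**The case against.** The strongest reply is that this rests largely on silence. Stating that numbers will be compared between arms gives the contrast, not the model. Covariates and the count distribution for one secondary outcome are commonly left to a statistical analysis plan, which is not shown. That stands: the article does not rule out adjustment, and an unseen plan may contain it. What the article does fix is a timeline without a baseline for an outcome whose hypothesis speaks of improvement.

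Table 2 also words its hypothesis for service delivery as a higher level in the intervention arm, which fits a follow-up comparison. So the mismatch is with section 1.1, not with the whole document.

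A reader might infer three stronger things, none of which the document supports:

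- **That the test is invalid without a baseline.** Allocation is randomised 1:1, so a comparison of post-allocation counts is unbiased.
- **That sessions from before allocation are counted and dilute the effect.** No passage says so. Follow-up is timed from baseline, and weekly tallies can be cut at any date. Only the start of the count is unstated.
- **That power would rise from about 50–53% to 77–89%.** Such figures come from treating sessions as an open-ended stream of about one per week at a constant rate per ASHA, with correlations of 0.55–0.77. That ignores the capped courses in section 2.3.2.

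Finally, the earlier data may not be entirely free to use. Section 2.3.2 points to the learning management system and Table 2 to the ASHAs themselves, and the length of the period before randomisation is not given.

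**Conclusion.** The point holds as a modest gain in precision on one secondary outcome and a mismatch between hypothesis (b) and its stated comparison. It is not a bias. For an effect that 122 per arm would detect with 80% power unadjusted, adjustment for the earlier session rate would give about 82% at rho 0.2 and 90% at rho 0.5, the range that seems likely with few patients per ASHA. At rho 0.1 the gain is negligible; 97.5% would need rho 0.7. These figures rest on an assumed correlation and a normal approximation in SD units, and the article states no power for this outcome. The unstated start of counting is a gap in the outcome definition and is worth closing whatever the correlation.

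**What to change.** In sections 2.4.2 and 2.8:

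- Define the outcome as HAP sessions delivered from each ASHA's randomisation date to 3 months and to 6 months.
- Compare arms with a count regression (negative binomial, or Poisson with robust standard errors) that adjusts for the ASHA's pre-randomisation weekly HAP session rate and the stratification factors, age and education.
- Report the rate ratio with its confidence interval.
- Do not use a raw change score.
- Reconcile the two data sources, and take the earlier rate from the same source as the outcome.

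If a comparable earlier rate cannot be obtained, reword hypothesis (b) as greater numbers at follow-up and keep the defined counting window.

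The cost is protocol or analysis-plan wording, using data that section 2.3.2 says are already retrieved. The small downside is that the period before randomisation is short and probably differs in length between ASHAs, which is why a weekly rate is needed and why it will be a noisy covariate.
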